# Cross-sectoral rehabilitation intervention for patients with intermittent claudication versus usual care for patients in non-operative management - the CIPIC Rehab Study: study protocol for a randomised controlled trial

**DOI:** 10.1186/s13063-019-4032-x

**Published:** 2020-01-21

**Keywords:** Intermittent claudication, Cross-sectoral rehabilitation, Physical exercise

## Abstract

**Introduction:**

Intermittent claudication (IC) caused by peripheral artery disease (PAD) is a common cardiovascular disease. Patients with IC have reduced walking capacity, restricted activity levels and mobility, and reduced health-related quality of life. The disease leads to social isolation, the risk of cardiovascular morbidity, and mortality. Non-operative management of IC requires exercise therapy and studies show that supervised exercise training is more effective than unsupervised training, yet many patients with IC lack motivation for changes in health behaviour.

No studies investigating the effects of existing cardiac rehabilitation targeted patients with IC have been published. The aim of this article is to present the rationale and design of the CIPIC Rehab Study, which examines the effect of a cross-sectoral rehabilitation programme versus usual care for patients in non-operative management for IC.

**Methods and analysis:**

A randomised clinical trial aims to investigate whether cardiac rehabilitation for patients with IC in non-operative management versus usual care is superior to treatment as usual. The trial will allocate 118 patients, with a 1:1 individual randomisation to either the intervention or control group.

The primary outcome is maximal walking distance measured by the standardised treadmill walking test. The secondary outcome is pain-free walking distance measured by the standardised treadmill walking test, healthy diet measured by a fat-fish-fruit-green score, and level of physical activity measured by an activity score within official recommendations. Statistical analyses will be blinded.

Several exploratory analyses will be performed. A mixed-method design is used to evaluate qualitative and quantitative findings. A qualitative and a survey-based complementary study will be undertaken to investigate patients’ post-discharge experiences. A qualitative post-intervention study will explore experiences of participation in rehabilitation.

**Discussion:**

The study is the first to assess the effect of a cardiac rehabilitation programme designed for patients with IC. The study will describe how to monitor and improve rehabilitation programmes for patients with IC in a real-world setting. Mixed-method strategies can allow for both exploration and generalisation in the same study, but the research design is a complex intervention and any effects found cannot be awarded a specific component.

**Trial Registration:**

Retrospectively registered in Clinicaltrials.gov identifier: NCT03730623.

## Background

Peripheral artery disease (PAD) is a chronic occlusive arterial disease caused by progressive atherosclerosis [1]. The most common symptom is intermittent claudication (IC), defined as a cramping leg pain that occurs during walking and is relieved by a short period of rest. IC affects 2% of the population (age 50–60) and increases with age to 6–7% (age 65–75) of the population in Western Europe and the USA [2]. Patients with IC have diminished walking capacity, restricted activity levels and mobility, and reduced health-related quality of life [3, 4]. It leads to social isolation and, unless health behaviour and relevant medications are prescribed, it may lead to worsening of disease with the risk of atherosclerotic complications and death [1, 3–8]. Motivation is an important but neglected factor as studies indicate that many patients with IC are not motivated for health behaviour changes in accordance with current recommendations [6, 7, 9]. Due to the risk of complications and limited patency of revascularisation (depending on procedure and anatomic location), current guidelines recommend that patients not requiring surgical revascularisation due to critical limp ischaemia be managed conservatively without surgical intervention [10]. Current practice for managing IC in Danish hospital settings involves brief advice to ‘stop smoking and keep walking’, combined with preventive medications including cholesterol-lowering treatment with statins and antiplatelet therapy [10, 11]. Non-adherence to these recommendations increases the risk of progression from IC to critical ischaemia and limb amputation [1]. It also produces a substantial economic burden on society due to reduced working ability, hospitalisation, and associated personal and social consequences for the individual patient [12, 13]. A recent Cochrane review [14] concluded that for patients with IC exercise is important regardless of whether treatment is revascularisation or overall conservative management. Supervised exercise training (SET) programmes are effective for alleviating symptoms, increasing walking distance, reducing cardiovascular risk factors and improving quality of life. Additionally, SET is relatively inexpensive and cost-efficient compared with other more invasive therapies [13–16]. Although evidence for SET is strong, studies exploring the effects of cross-sectoral rehabilitation intervention on patients treated for IC are lacking. IC rehabilitation is still poorly implemented and knowledge about how to set up an effective programme in a community-based setting is poor [17, 18].

### Rehabilitation

Secondary prevention initiatives including rehabilitation for patients with PAD are recommended in current guidelines [5, 19]. Community-based supervised exercise appears to be at least as effective as exercise programmes provided in hospital settings [20]. Importantly, a study recently reported that attending a hospital-based supervised exercise programme was difficult for patients due to time spent on transportation and logistics [21]. This indicates that intervention in the local community improves patients’ motivation and adherence [22]. Therefore, given the evidence for the beneficial effect of supervised exercise training for patients after acute coronary syndrome, the hypothesis is that patients with IC could also benefit with regard to maximal walking distance (MWD), pain-free walking distance (PWD), health-related quality of life, and physical function. Patients' perspectives on participating in the intervention could shed light on the factors that facilitate or hinder exercise and recommended health behaviour. Knowledge of this may increase both the quality and patient adherence to the conservative management of IC, thereby attenuating the burden of disease and improving quality of life for patients with IC.

## Study objectives

The objectives of the trial are to investigate the effects of a cross-sectoral exercise and lifestyle intervention based on the established rehabilitation programme for patients with ischaemic heart disease versus usual care without rehabilitation in patients with IC. The primary hypothesis is that, compared with the control group, a specialised rehabilitation programme for the intervention group improves MWD in the treadmill walking test after the completed intervention. The three secondary hypotheses are that PWD, diet and level of physical activity improve in the intervention group compared with the control group after 6 and 12 months. Exploratory analyses will test the hypothesis that IC rehabilitation improves quality of life, health behaviour, physical activity and reduces anxiety and depression after 6 and 12 months. The effects, benefits, and motivational factors of conservative management will be examined and patient experiences of the intervention, including factors that support or hinder adherence to the intervention explored.

## Design

The CIPIC Rehab Study is designed to develop evidence-based knowledge on rehabilitation among patients with IC. It is a cross-sectoral, multidisciplinary, randomised clinical trial designed to examine the effects of an IC rehabilitation programme compared with usual care for patients in non-operative treatment for IC. Accordingly, the trial combines quantitative and qualitative research methods. The mixed methods are integrated by applying the explanatory sequential design [23, 24]. The rationale for this approach is that the quantitative findings provide a general understanding of the research problem through statistical results, and qualitative findings refine and explain the results by exploring participants’ views in greater detail. Qualitative research coupled with randomised controlled trials can contribute to developing and evaluating complex healthcare interventions; it may be particularly useful in evaluating interventions that involve social and behavioural processes that are difficult to explore or capture using quantitative methods alone [25, 26]. A pragmatic world view is the philosophy underpinning the study [23].

### Study population and eligibility criteria

Consecutive patients at the Department of Vascular Surgery at the Rigshospitalet in Copenhagen, Denmark will be screened for inclusion and approached for study participation.

Inclusion criteria are: patients with newly diagnosed IC treated conservatively; age > 18 years; speak and understand Danish; able to provide informed written content; citizens of the eight municipalities of Greater Copenhagen belonging to the Healthcare Centre; and able to perform physical exercise. Exclusion criteria are: failure to understand and cooperate according to the trial instructions; co-morbidity complicating physical activity and exercise training, and lack of informed content.

### Study procedure

When the informed content is signed, baseline data will be collected including a questionnaire administrated by the primary investigator. After baseline data collection, randomisation is conducted. Computer-generated block randomisation in four blocks has been done by an independent statistician and delivered in envelopes blinded from investigators. Randomisation is conducted by ongoing inclusion numbers marked on the envelopes.

### Control group – usual care

Patients randomised to the control group will initially receive the department’s usual, brief advice about exercise therapy (walking), smoking cessation, and preventive medical treatment with antiplatelet therapy and statins. The IC patients will receive written information about medication, walking exercise, and a logbook for self-reporting of walking behaviour in the outpatient clinic at the Department of Vascular Surgery, Rigshospitalet. Patients in the control group will follow standard follow-up procedure for patients treated for IC.

### Experimental intervention group

The intervention group initially receives the usual care in the outpatient clinic at the Department of Vascular Surgery; additionally, patients’ home communities offer courses in smoking cessation. Patients will receive a pedometer and be asked to self-report walking behaviour and steps in a logbook. The patient brings the logbook to the consultation with the physiotherapist, who initiates the startup training, supplies the motivation and explains the goal for the physical activity. Patients in the intervention group will follow the specialised cardiac rehabilitation programme for patients with IC. The intervention is based on experiences of cardiac rehabilitation and guidelines of the Danish National Board of Health and European Society of Cardiology [19]. Theories about personalised feedback and self-efficacy will be used as a method for encouraging behavioural changes to improve health outcomes [27].

### Physical exercise training component

Training sessions will take place at a Healthcare Centre within the municipality of Greater Copenhagen. The main goal of the exercise is to improve the patient’s physical capacity and health behaviour, such that this subsequently results in physical and psychological health benefits. Supervised exercise training is also targeted, relieving the fear and uncertainty the patient may feel towards physical activity. Two specialised cardiac rehabilitation physiotherapists with specific insight into IC will plan and supervise participants’ exercise. This entails patients actively engaging, in groups with up to ten in 24 supervised physical exercise sessions, each lasting one hour with two weekly sessions. The exercises include varied forms of physical exercise all combined to accommodate the patients’ own goals regarding walking distance. The physiotherapists will administer and record a six-minute walking test and 30-second chair stand test prior to and at completion of the intervention. Pedometer and self-reported walking behaviour are a part of the consultation used to increase or sustain daily physical exercise at least 30 minutes per day. The results will be used as part of an individual motivational interview with each patient after completion of the 24 training sessions.

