### Qualitative explorative data

As a part of the study, brief individual interviews exploring course satisfaction, suggestions for changes, and the relevancy of the various rehabilitation components will be conducted. Furthermore, focus group interviews of patients participating in the intervention group will also be conducted. Prior to interviewing, an interview guide will be developed. It will be used to help explore patient experiences of training and teaching sessions, factors helping or hindering improvement in health behaviour, the use of the pedometer, logbook, and text message influenced motivation/adherence, patient satisfaction with the intervention and suggestions for future rehabilitation programmes. Research questions will be developed using knowledge from existing qualitative studies in the field and the individual brief interviews [6, 7, 9, 15, 17, 50, 51] (see Table 2). The focus group interviews will be conducted by the principal investigator (MS) and two assistant moderators that register key points and takes field notes [52]. Patients will be recruited during their 3- and 6-month follow-ups at the Healthcare Centre or at the Department of Vascular Surgery as a convenience sampling with consecutive recruitment of participants according to the groups in which they exercised during the training sessions. To embrace the potential impact of any team spirit developed during the training session, we consider focus groups and recruitment of participants according to training groups to be relevant. The interviews will be held in well-known surroundings in the Healthcare Centre. The size of the focus groups will be five to eight participants to secure an opportunity for each person to share insights, experiences and observations. Smaller groups allow more in-depth conversation and afford each person a greater opportunity to speak. ‘Information power’ will guide the adequate sample size and the number of focus group interviews [52].

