## Statistical analysis

A trial-independent statistician will make a blind analysis of the data and the primary and secondary analyses will be performed according to the intention-to-treat principle. We will use general regression models for the continuous outcomes and logistic regression models for binary outcomes. In the analysis of the primary outcome, the outcome (MWD at 6 months) will be analysed with adjustment for baseline MWD, sex or age (included continuously). For the three secondary outcomes – PWD distance, level of physical activity and diet at 6 months – the analysis will be done similarly with adjustment for baseline values, sex and age (continuous). As exploratory analyses of MWD, PWD, smoking behaviour, diet and patient-related outcome measures, mixed general and generalised models with repeated measurements will be used including measurements at baseline, 6 and 12 months in the same model. These models will also be used for all other explorative outcomes. In these models, the interaction between intervention group and time is of primary interest, indicating different developments after intervention start. In the case of significant results in the primary outcome, sensitivity analyses will be performed to estimate the potential effect of data missing at random by a worst-case scenario. Let X be the group where a beneficial effect is observed, and Y be the other group. Missing values in group X will be imputed by the minimum value found in the material and missing values in group Y will be imputed by the maximum value found. The primary outcome will be tested first using a significance level of 0.05. Analyses of the secondary and exploratory outcome measures as planned above will be analyzed with no *p* value adjustment due to multiplicity. Instead, the interpretation of these results will be assessed in the light of multiple testing, i.e. statistically significant effects will be interpreted in the context of increased risk of type I error. The clinical effect size will be reported by Cohen’s d. Per protocol analyses of the primary and secondary outcomes will be performed.

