### Sample size and power calculation

The expected average baseline value of MWD has been set to 120 m with a detected 50% improvement (60 m). There is a wide variance in MWD in this patient group and consequently the standard deviation (SD) is set at 100 m, based on an expected improvement in walking ability of approximately 50% to 200% [18]. With a 5% significance level and 80% power, it will thus be necessary to include 88 patients to detect an improvement of 60 m in MWD in the intervention group at the 12-month follow-ups, compared with the control group. Owing to the previously mentioned risk of co-morbidities, combined with an expected drop-out, a drop-out of 25% must be expected, therefore the investigators plan to include 118 patients in total (59 in each group).

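### Only the intervention arm is treated in shared training groups, but the primary model and the sample size assume independent patients in both arms

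*Protocol article*

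**What the plan says.** The protocol article randomises individuals: "The trial will allocate 118 patients, with a 1:1 individual randomisation to either the intervention or control group". Grouping begins after randomisation and in one arm only. Under Physical exercise training component, intervention patients train "in groups with up to ten in 24 supervised physical exercise sessions", twice weekly, supervised by two physiotherapists. The next two sections add team relay races, group dialogue on motivation, and group sessions with a nurse and a dietician. Education in groups and individual consultation counts the group among the things that matter in rehabilitation. Under Control group – usual care, controls receive brief advice, written information and a logbook; no groups are described.

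Under Qualitative explorative data, focus groups are to be recruited by training group, and the reason given is "To embrace the potential impact of any team spirit developed during the training session".

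Under Statistical analysis, the plan is: "We will use general regression models for the continuous outcomes and logistic regression models for binary outcomes". The named covariates are patient-level (baseline value, sex, age). Mixed models appear only for exploratory repeated measurements. No training-group term is named.

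Under Sample size and power calculation: "With a 5% significance level and 80% power, it will thus be necessary to include 88 patients", with the target "to detect an improvement of 60 m in MWD in the intervention group at the 12-month follow-ups, compared with the control group". The variability is fixed as follows: "consequently the standard deviation (SD) is set at 100 m". Neither an ICC nor a design effect appears.

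**The concern.** This is a partially nested design: outcomes in one arm may be correlated through shared sessions and peers, while outcomes in the other arm are not. Individual randomisation does not remove dependence that arises afterwards during delivery. A regression that treats all patients as independent then gives too narrow an interval for the primary effect and rejects a true null hypothesis more often than the declared 5%. The sample size rests on the same assumption, so its 80% power applies to a valid test only if there is no correlation within groups. At stake is a primary result near the significance boundary that would not survive an analysis allowing for the groups.

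**Working it through.** **Inputs from the protocol article.** Difference 60 m, SD 100 m, significance level 5% (taken as two-sided; the article does not say), power 80%, drop-out 25%, 1:1 allocation, 59 randomised per arm, training groups of at most ten.

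**Assumed, because the article does not give them.** The ICC (0 to 0.10); the number m of analysed patients per training group (5 to 10; about 7 if 44 analysed patients fall into about six groups); closed groups; equal total variance in both arms.

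**Step 1: reproduce the plan's figure.** For independent patients, n per arm = 2 × [100 × (1.960 + 0.842)/60]² = 43.6, so 44 per arm and 88 in total. Drop-out: 88/0.75 = 117.3, so 118. Both figures match. The standard error is 100 × √(2/44) = 21.3 m and the power is Φ(60/21.3 − 1.96) = 80.4%. The calculation therefore holds no allowance for grouping and none for baseline adjustment.

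**Step 2: allow for groups in one arm.** The design effect in the intervention arm is DE = 1 + (m − 1) × ICC. The true standard error is 100 × √[(DE + 1)/44], and its ratio to the planned one is R = √[(DE + 1)/2]. An analysis that ignores the groups has type I error 2 × [1 − Φ(1.96/R)]. The power of a valid analysis, without baseline adjustment and before any small-sample correction, is Φ(60/SE − 1.96).

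For example, m = 7.5 and ICC = 0.05 give DE = 1 + 6.5 × 0.05 = 1.325, R = √(2.325/2) = 1.078, SE = 23.0 m, type I error 6.9% and power 74.2%.

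| ICC (assumed) | Type I error, m = 5 | m = 7.5 | m = 10 | Unadjusted power, m = 5 | m = 7.5 | m = 10 |
|---|---|---|---|---|---|---|
| 0 | 5.0% | 5.0% | 5.0% | 80.4% | 80.4% | 80.4% |
| 0.01 | 5.2% | 5.4% | 5.5% | 79.6% | 79.1% | 78.6% |
| 0.02 | 5.5% | 5.8% | 6.1% | 78.8% | 77.8% | 76.9% |
| 0.05 | 6.2% | 6.9% | 7.7% | 76.5% | 74.2% | 72.0% |
| 0.10 | 7.4% | 8.9% | 10.4% | 72.9% | 68.6% | 64.7% |

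Simulating an ordinary t-test with six groups of 7 gives a type I error of about 5.6%, 6.8% and 8.5% at ICC 0.02, 0.05 and 0.10, in line with the formula.

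**Step 3: bring in the planned baseline adjustment.** With an assumed correlation r between baseline and follow-up, the variance is multiplied by 1 − r². At m = 7.5, with the ICC applied to the adjusted residuals:

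- r = 0.3: power 84%, 78% and 73% at ICC 0, 0.05 and 0.10.
- r = 0.5: power 90%, 85% and 81%.

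The type I error does not improve, because R depends only on DE. It can get worse if adjustment removes individual variance but leaves the group variance. With r = 0.5, an ICC of 0.05 becomes 0.05/0.75 = 0.067, DE = 1 + 6.5 × 0.067 = 1.43, and the type I error is about 7.6%.

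**The case against.** The case against has several sound parts.

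- **No ICC is given, and it may be near zero.** Two physiotherapists supervise the whole arm, which limits one usual source of differences between groups. Exercise is tailored to each patient's goals and limits. The 24 sessions end after about 12 weeks, and the primary outcome comes at 6 months, so a group effect could fade. This stands: the harm is conditional. Shared staff do not remove peer effects, however, and the article itself counts the group as important.
- **The groups may not have been closed.** Inclusion ran from 5 December 2017 to 28 June 2019, 570 days or 81.4 weeks. If 59 patients entered evenly, that is 0.72 per week, and 12 × 0.72 = 8.7 would be in a 12-week programme at any time. One rolling class of up to ten fits as well as six cohorts. This stands, and the fix must allow for it.
- **An analysis plan could add a group term.** It could. But the article states its covariates and its sample size, and both rest on independence.

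A reader might infer that the protocol expects a team-spirit effect on walking distance. It does not: it speaks of a potential impact, and only to justify how focus groups are formed. A reader might also infer that the standard errors are known to be too small. That needs a positive ICC, which the document neither gives nor rules out.

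**Conclusion.** The point holds as a conditional weakness in the analysis, not as a proven error in power. Delivery is grouped in one arm, and neither the stated primary model nor the sample size allows for it. With about 7 analysed patients per group, the type I error of the planned analysis would be about 5.6-6% at an ICC of 0.02, 7% at 0.05 and 8.5-9% at 0.10. At 0.01 or below the change is negligible. These figures rest on an assumed ICC, an assumed group size and closed groups. Baseline adjustment does not repair the standard error.

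It is tempting to replace the stated 80% power with 70-78%. The document does not support that: those figures leave out the planned baseline adjustment, which at a correlation of 0.5 would keep power above 80% even at a residual ICC of 0.10, though not at a correlation of 0.3. What can be said is that 80% holds only under independence and without baseline adjustment.

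**What to change.** Inclusion is complete, so the remedy lies in the analysis and not in the number of patients.

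1. Record the training group of each intervention patient in the trial data. The focus-group plan treats groups as identifiable, but the article does not say that membership is recorded.
2. For maximal and pain-free walking distance, prespecify a partially nested model: a random group intercept in the intervention arm only, with small-sample degrees of freedom (Satterthwaite or Kenward-Roger). At the least, make it a sensitivity analysis that must support the primary conclusion.
3. For binary outcomes, use a method suited to few clusters; those degrees-of-freedom corrections do not carry over to logistic regression.
4. If entry was rolling, define the group by the main training cohort or use a multiple-membership term.
5. Report the ICC. State that 80% power assumes independence and no baseline adjustment, and show power over a range of ICC values (unadjusted, 7.5 per group: about 78%, 74% and 69% at 0.02, 0.05 and 0.10), noting that baseline adjustment may offset the loss.

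The work is some wording, one variable and one random effect. The statistical cost is a wider interval and, with about six groups, an imprecise group variance that may be estimated as zero. As a cautious guide to that cost, an unadjusted simulated analysis of six group means against 44 controls had about 75% power at ICC 0, 68% at 0.05 and 62% at 0.10, with type I error near 5%. That price is a reason to accept the nested model as a sensitivity analysis.
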